### Participant timeline {13}

Participant timeline: schedule of enrolment and interventions

**Table Tabb:** 

	**Trial period**				
	**Enrolment**		**Post-randomisation (after trial entry)**		**Close-out**
**Timepoint**	Within 24 h of birth		Immediately post-randomisation	At hospital discharge	At 1 year of age^a^
**Enrolment**					
Eligibility assessment	X				
Informed consent^c^		X			
Randomisation		X			
Intervention/comparator					
Intervention — surfactant administration^b^			X		
Comparator — expectant management (non-invasive respiratory support)			X		
Assessments					
Questionnaires (EQ-5D-5L; feeding)^c^			X	X	
Perinatal clinical data collection			X	X	
Follow-up data collection using routine national databases					X
Adverse events assessments (SAEs, SUSARs)			X	X	

^a^Corrected for prematurity

^b^Surfactant for infants randomised to early surfactant therapy will be administered as soon as possible after randomisation

^c^Provide questionnaire for completion only if the mother has provided consent to participate

### Sample size {14}

One of the primary outcomes is the length of hospital stay from trial entry to discharge home. Reported length of stay for late preterm infants with respiratory distress is estimated to be between 10 and 15 days from the literature [4, 10, 18]. Calculations are based on the reduction in median length of stay in NNU from 12 to 10 days in the early surfactant versus expectant management group. To detect a 2-day reduction in the length of stay (equivalent to a hazard ratio of 1.2) with 90% power and a two-sided 5% significance level, a total sample size of 1280 is required. We estimate the prevalence of multiple births in our patient population to be 25% [19] with an intra-class correlation coefficient of 0.9, based on previous perinatal trials. Allowing for an inflation factor of 1.13 for this and a 5% attrition rate, the required recruitment target is 1522 (761 per group). Based on data from NNUs, around 40–50 late preterm and early term infants per year require respiratory support. We aim to recruit an average of two infants per month over 30 months in approximately 45 NNUs to reach the target sample size of 1522, allowing for a staggered start.

The other primary outcome is the proportion of infants who reach a predefined higher threshold of disease severity, at which clinicians may choose to give ‘rescue’ surfactant. A recent study [20] reported an event rate of 45% in a cohort of late preterm infants admitted to neonatal intensive care for respiratory failure. This is likely to be lower in the trial population, which also includes early term infants. With a sample size of 1522, a treatment difference of 9% could be detected with 90% power and a two-sided 5% significance level if the expectant management group event rate was 45%. A smaller treatment difference could be detected if the expectant management group event rate (CER) was lower than this (e.g. 8% difference for a CER of 35%, 7% difference for a CER of 25%).

### Recruitment {15}

Given the estimated annual rate of late preterm and early term infants requiring respiratory support in participating NNUs, it is anticipated that an average of two infants per month can be recruited over a 30-month period. This will allow for a staggered start across the participating centres to reach the target sample size.

The SurfON trial aims to achieve adequate participant enrolment by implementing a multipronged recruitment strategy targeting potential participants (parents of eligible infants and pregnant women).

Each site will maintain a screening log of all infants reviewed for eligibility, including those deemed ineligible and those whose parents decline participation. This systematic record allows monitoring of recruitment activity and identifies potential barriers to enrolment.Early engagement is an important component of the recruitment strategy. With the agreement of clinical teams, women expected to deliver between 34 and 36 weeks’ gestation may be screened for eligibility prior to birth. This enabled early identification of potential participants and maximised the available time to parents to consider participation. This approach helped to identify potential participants early and ensured that eligible infants were not missed due to time constraints immediately after delivery. In addition, clinicians were encouraged to approach parents of infants showing early signs of respiratory distress even before all eligibility criteria were fully met. This gave families additional time to consider the study and to make an informed decision should their infant’s condition progress to require noninvasive respiratory support.Awareness of the trial will be promoted using a variety of informational and recruitment materials. Posters, banners, and leaflets will be displayed in neonatal units to raise awareness among both staff and parents. These will be supplemented by other resources, including podcasts and parent-facing information leaflets, to support understanding of the trial and encourage participation. Together, these approaches aim to maximise trial visibility, ensure families are well informed, and facilitate sustained recruitment across all participating sites.

## Assignment of interventions: allocation

### Sequence generation {16a}

The allocation sequence will be generated by a bespoke system developed using the programming language PHP and database MySQL.

The randomisation programme will use a minimisation algorithm to ensure balance between the treatment groups with respect to week of gestation at birth, multiple birth, and centre. Infants will be randomised in a 1:1 allocation ratio to either the early surfactant therapy or expectant management group. Twins or higher-order multiple births will be randomised to the same arm.

### Concealment mechanism {16b}

A Senior Trials Programmer at the National Perinatal Epidemiology Unit (NPEU CTU) will write the randomisation programme and hold the treatment allocation codes. The randomisation programme will be hosted on a secure web-based platform. The IMP will be dispensed from the hospital stock through routine prescription. The senior trials programmer and trial statisticians will monitor the implementation of the randomisation procedure throughout the trial. Reports will be provided to the Data Monitoring Committee (DMC).

### Implementation {16c}

Randomisation of infants will be managed through a secure web-based randomisation facility hosted by the National Perinatal Epidemiology Unit Clinical Trials Unit (University of Oxford). Telephone backup will be available 24/7.

Randomisation will occur as soon as possible after eligibility is confirmed and informed consent is obtained. Staff at recruiting sites will log in to this system using a unique centre login to randomise participants. The system will prompt users to enter data to confirm eligibility, assign a unique SurfON trial identification (ID), and specify the randomised allocation for the infant.

For infants randomised to the early surfactant therapy group, surfactant administration should occur as soon as possible after randomisation.

## Assignment of interventions: blinding

### Who will be blinded {17a}

As SurfON is an open-label trial, participants and treating clinicians will not be blinded to treatment allocation. A validating statistician, who will remain blinded to treatment allocation, will independently check and confirm the primary comparative analyses after database lock. Full blinding of the trial statisticians is not possible, as interim reporting to the Data Monitoring Committee (DMC) requires an unblinded statistician to prepare safety and feasibility summaries. To limit potential bias, interim reports will be restricted to descriptive summaries only, without inferential comparisons between trial arms.

### Procedure for unblinding if needed {17b}

Not applicable as SurfON is not a blinded trial.

## Data collection and management

### Plans for assessment and collection of outcomes {18a}

Prior to any data collection, the mother must provide informed consent. Once consent is obtained, the randomisation process is initiated by filling out the appropriate forms on the SurfON randomisation website where the infant will be allocated *to early surfactant therapy* or *expectant management*.

Data for the SurfON study will be collected primarily on electronic case report forms (eCRFs) within the OpenClinica clinical database. Mandatory CRFs include the consent form (paper), randomisation, contact details, trial entry, trial intervention, respiratory support log, outcomes, and mother’s entry and discharge questionnaire (if consent is provided). Additional CRFs may be required for certain participants, such as the surfactant, hospital transfer, withdrawal, SurfON serious adverse event, and SurfON incident and deviation forms. These forms will be completed as needed.

Outcome data will be collected primarily from existing hospital records and electronic data collection systems. Data will be entered on trial-specific CRFs by site staff, with the outcome CRF completed at hospital discharge. Optional questionnaires may be administered to mothers who have consented, assessing quality of life and breast milk feeding. Maternal quality of life will be assessed using the preference-based EQ-5D-5L instrument. If an infant is transferred to another hospital, the recruiting site will remain responsible for data collection.

Secondary care use and survival data will be obtained from available electronic national databases in the UK. Databases will include information on hospital inpatient admissions, outpatient visits, paediatric critical care, and mortality data. This will include Hospital Episode Statistics (HES) in England and the electronic Data Research and Innovation Service (eDRIS) in Scotland. Parental consent will be obtained at trial entry to allow for follow-up using routine national databases.

### Plans to promote participant retention and complete follow-up {18b}

The Trial Co-ordinating Centre will maintain regular contact with all sites to ensure accuracy and completeness of all study documentation during the infants’ participation in the study. For infants who discontinue participation or where there is a deviation from protocol after the point of randomisation, sites will be asked to record reasons for this and to continue data collection for analysis of outcomes according to intention to treat.

Source data verification (SDV) is performed on the first 10 completed respiratory logs from each site, which record the primary outcome for the trial. Data are entered directly into OpenClinica, and paper copies are provided to the trial team for SDV checks. The trial team conducts manual SDV checks, provides individual feedback to sites, flags errors, and sends detailed emails highlighting common mistakes to prevent future errors. Additionally, the trial team hosts webinars, refresher training sessions, and drop-in sessions to address concerns and clarify proper completion of respiratory logs.

### Data management {19}

The Data Management Plan will outline the detailed procedures for data collection, cleaning, validation, and analysis to ensure the production of high-quality data for statistical analysis.

Source documents are where data are first recorded and from which infants’ CRF data are obtained. CRF entries will be considered source data if the CRF is the site of the original recording.

Authorised representatives from the sponsor, funder, research team, NHS trust, and regulators will have direct access to data for monitoring and auditing. Site staff will have restricted, password-protected access to the clinical database.

Clinical data will be entered into a validated database, with validation checks for accuracy. Participant names and identifiable information will be stored in a separate administrative database.

Electronic and paper records will be stored securely, with restricted access to authorised personnel. Electronic files will be stored on a secure server, with regular backups and restricted entry. Archiving of the Trial Master File will follow the requirements of the Clinical Trials Regulations, NPEU CTU Standard Operating Procedures, and applicable regulations, with a review of further archiving needs based on data protection laws. Data will be retained at recruiting sites in line with applicable NHS and trust policies.

At the end of the trial, all participant data will be transferred to the University of Leicester for long-term follow-up, in compliance with data sharing agreements.

### Confidentiality {27}

The trial will adhere to strict data privacy regulations, including the General Data Protection Regulation (GDPR) and Data Protection Act 2018. All documents will be stored securely at the NPEU CTU and accessible only to authorised trial staff. Personal identifiers and trial data will be stored in separate databases linked by the infant’s trial number. After the trial is completed and reports are published, data will be archived in a secure location with controlled access.

### Plans for collection, laboratory evaluation and storage of biological specimens for genetic or molecular analysis in this trial/future use {33}

Not applicable as there is no lab involvement.

## Statistical methods

### Statistical methods for primary and secondary outcomes {20a}

#### Primary outcomes

The statistical analysis will be conducted according to a pre-specified statistical analysis plan (SAP), which will be available in a separate document. The SAP will provide detailed information on the methods used to analyse the primary and secondary outcomes, including any adjustments for covariates and multiple comparisons.

Infants will be analysed in the groups to which they were randomly assigned, regardless of protocol deviations or actual treatment received (intention-to-treat (ITT) analysis population).

The primary analysis will be adjusted for minimisation factors (week of gestation at birth, multiple birth, and centre). The correlation in outcomes between multiple births will also be adjusted for, where technically possible.

For the length of hospital stay primary outcome, a time-to-event analysis using a Cox proportional hazards model will be conducted to calculate the hazard ratio and 95% confidence interval (CI). Kaplan–Meier curves will be plotted to visualise the survival functions. Median length of stay with interquartile ranges will be reported for each group. Deaths will be excluded (not censored) from the time-to-event analysis and reported separately.

For the severe respiratory failure primary outcome, risk ratios with 95% CI will be calculated using log-binomial regression or Poisson regression with a robust variance estimator in the event of non-convergence. Absolute risk difference and associated confidence intervals will also be calculated. 95% confidence intervals will be used for all comparative analyses, including subgroup analyses. *p*-values will be presented for the primary outcome comparisons with a two-sided 5% level of significance used for statistical inference. There will be no adjustment made for multiplicity when testing the two primary outcomes. Careful interpretation of the results will be based on the following: If both primary outcomes show evidence of superiority (i.e. evidence to reject the null hypotheses for both primary outcomes), this will be interpreted as providing robust evidence that early surfactant therapy is superior to expectant management. Similarly, if results show no evidence of a difference for both primary outcomes, this will be interpreted as providing no evidence that early surfactant therapy is superior to expectant management. In all other scenarios, the results will be interpreted cautiously and in the context of corroborating evidence from the secondary outcomes.

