### Eligibility criteria {10}

#### Inclusion criteria

Born at 34^+0^ to 38^+6^ weeks of gestation ≤ 24 h oldRespiratory distress defined as follows:*FiO*_*2*_ ≥ 0.3 and < 0.45 needed to maintain *SaO*_*2*_ ≥ 92%*FiO*_*2*_ < 0.3 with clinically significant work of breathingClinical decision to provide noninvasive respiratory supportWritten parental informed consent

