### Outcomes {12}

The primary and secondary outcome measures are detailed in Table 2.

**Table 2 Tab2:** Primary and secondary outcome measures

**Outcome measures**	**Time point(s) of evaluation of this outcome measure**
•*Length of infant’s hospital stay* after birth, defined as the number of days from birth to discharge home from hospital	Between birth and discharge home from hospital
•*Incidence of severe respiratory failure*, defined as sustained (≥ 30 min) requirement for *FiO*_*2*_ ≥ 0.45 to maintain oxygen saturations (SaO_2_) ≥ 92%	Between trial entry and discharge home from hospital
**Perinatal clinical outcome measures**	**Time point(s) of evaluation of this outcome measure**
•*Total duration of NNU stay*, defined as total number of days of inpatient care in a neonatal unit (defined according to Healthcare Resource Group (HRG) Critical Care categories 1–5, 2016)	Between trial entry and infant discharge home from hospital
•*Total duration of neonatal intensive care*, defined as number of days of neonatal intensive care (defined according to HRG Critical Care categories 1–5, 2016)	
•*Duration of mechanical ventilation*, defined as days of ventilation via an ETT (endotracheal tube)	
•*Duration of noninvasive respiratory support*, using positive airway pressure or high flow	
•*Pulmonary air leaks*, requiring insertion of a chest drain	
•*Days of mother-infant separation*, defined using HRG Critical Care categories 1–5, 2016	
•*Breast milk feeding*, defined as (a) any breast milk feeding during neonatal hospital stay, (b) any breast milk feeding at hospital discharge, and (c) exclusive breast milk feeding at hospital discharge	
•*Late onset sepsis*, defined as the incidence of *microbiologically confirmed or clinically suspected* invasive infection more than 72 h after birth	
•*Need for inhaled nitric oxide (iNO) therapy*	
•*Need for extracorporeal membrane oxygenation (ECMO)*	
•*Medical respiratory diagnoses*, defined as any respiratory diagnosis attributed to the infant	
•*Surfactant administration*, defined as (a) administration of any additional surfactant in infants randomised to receive early surfactant or (b) administration of any surfactant in infants receiving expectant management, including number of doses and dose given	
•*Maternal length of hospitalisation*, defined as the total number of days spent by the mother in hospital after trial entry	Between trial entry and maternal discharge home from hospital

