#### Secondary outcomes

For binary outcomes, risk ratios and 95% CIs will be estimated, following the same planned analysis as for the severe respiratory failure outcome. For normally distributed continuous outcomes, mean or median differences with 95% CIs will be calculated using linear regression. If the data show significant skewness, median differences with 95% CIs will be calculated using quantile regression. As per the primary outcomes, both crude and adjusted estimates will be presented, but the primary inference will be based on estimates adjusted for minimisation factors.

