### Methods for additional analyses {20b}

#### Subgroup analyses

Pre-specified subgroup analyses will be conducted to examine the consistency of the effect of the intervention across gestational age groups (late preterm vs. early term) and first type of noninvasive respiratory support given (high flow vs. positive airway pressure) using the statistical test of interaction. 95% confidence intervals with a two-sided 5% level of significance for statistical inference will be presented.

No sensitivity analyses have been specified.

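### The primary model for severe respiratory failure omits FiO2 at randomisation, the baseline value of that outcome's own scale, and so gives up some precision

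*Protocol article*

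**What the plan says.** Under Statistical methods, Primary outcomes {20a}, the adjustment set is given as a list: "The primary analysis will be adjusted for minimisation factors (week of gestation at birth, multiple birth, and centre"). Under Secondary outcomes the article adds that, as for the primary outcomes, "the primary inference will be based on estimates adjusted for minimisation factors".

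The list matches the allocation scheme in Sequence generation {16a}, where minimisation seeks "balance between the treatment groups with respect to week of gestation at birth, multiple birth, and centre".

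FiO2 appears in two other places:

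- **Inclusion criteria {10}.** One route into the trial is FiO2 "≥ 0.3 and < 0.45 needed to maintain" the target saturation. The other is FiO2 below 0.3 with clinically significant work of breathing.
- **Outcomes {12}, Table 2.** The second primary outcome is "Incidence of severe respiratory failure*, defined as sustained (≥ 30 min) requirement for" FiO2 of 0.45 or more.

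Under Implementation {16c}, "The system will prompt users to enter data to confirm eligibility" before the allocation is given. Under Subgroup analyses {20b}, "No sensitivity analyses have been specified", and FiO2 is not one of the two subgroup variables.

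**The concern.** Entry FiO2 is the baseline value of the variable on which severe respiratory failure is defined. An infant who enters at 0.44 is one step from the threshold; an infant who enters at 0.22 is not. A covariate of this kind would usually be among the first candidates for a primary model. Because eligibility depends on it, it has to be known before randomisation. Nothing in the article balances it or adjusts for it.

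What is at stake is efficiency. If entry FiO2 is prognostic, leaving it out leaves explainable variance in the comparison. This matters most where power is thinnest. The sample size section expects an event rate below 45%, and its power figures for this outcome use the full 1522 infants without the allowance for multiples and attrition that it makes for length of stay.

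**Working it through.** **1. The plan's own figures (Sample size {14}).**

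- Length of stay: a hazard ratio of 1.2, 90% power and two-sided 5% need 1265 events (Schoenfeld) or 1272 (Freedman), close to the stated 1280. Then 1280 × 1.13 / 0.95 = 1522.5, the stated 1522.
- Severe respiratory failure: the stated 90% or so holds at 761 per arm. Removing the same inflation and attrition leaves an effective 1280 / 2 = 640 per arm.

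| Control vs surfactant | Power, 761 per arm | Power, 640 per arm |
|---|---|---|
| 45% vs 36% | 94.8% | 90.7% |
| 35% vs 27% | 92.2% | 87.3% |
| 25% vs 18% | 91.4% | 86.3% |

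None of these figures relies on FiO2 adjustment, so omitting it does not undermine the stated sample size.

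**2. Gain with continuous FiO2.** The prognostic strength is an assumption. Trials of 1280 infants were simulated with a standard-normal baseline covariate. The risk difference was estimated with and without linear adjustment, using robust standard errors.

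| Odds ratio per SD | Power, 45% vs 36%: without → with | Power, 25% vs 18%: without → with |
|---|---|---|
| 1.25 | 90.8% → 91.2% | 87.2% → 87.3% |
| 1.5 | 90.8% → 92.0% | 86.8% → 87.3% |
| 2.0 | 90.5% → 93.2% | 86.5% → 88.9% |
| 3.0 | 89.8% → 94.9% | 86.1% → 89.7% |

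Variance explained rises from about 1% to 20% in the 45% case and from about 1% to 17% in the 25% case. Unadjusted power differs between rows only through simulation error.

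**3. Gain with the eligibility stratum only.** Assume a 50:50 split between entry routes (q = 0.5), with risks pL and pH and mean risk p = 0.30. Then R² = q(1−q)(pH−pL)² / [p(1−p)].

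- 20% vs 40%: 0.25 × 0.04 / 0.21 = 4.8%
- 15% vs 45%: 0.25 × 0.09 / 0.21 = 10.7%
- 10% vs 50%: 0.25 × 0.16 / 0.21 = 19.0%

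The equivalent in extra infants is N × [1/(1−R²) − 1]. On the full 1522 this gives about 76, 183 and 358. On the effective 1280 it gives about 64, 154 and 301, which is the fairer base. These R² values are marginal. The increment over week of gestation and centre, which are already in the model, will be smaller.

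Simulating the planned Poisson model with robust variance at 1280 infants, with this stratum as the only covariate, gives:

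- Control rate 25%: strata 15/35%, about 87% → 88%; strata 10/40%, about 86% → 89%.
- Control rate 35%: strata 25/45%, about 87% → 88%; 20/50%, about 87% → 90%; 15/55%, about 87% → 91%.

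**4. Chance imbalance.** With q = 0.5 and 761 per arm, the 95% limit on the difference in the high-FiO2 share is 1.96 × √(2 × 0.25 / 761) = 0.050. Multiplied by risk gaps of 0.20 to 0.40, this shifts the risk difference by 1.0 to 2.0 points at that limit. In the continuous simulation at a 45% control rate, the shift has mean zero and a standard deviation of 0.3 to 1.2 points.

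**5. Length of stay.** If 1.2 is the hazard ratio conditional on FiO2, and FiO2 carries a hazard ratio of 1.1, 1.25, 1.5 or 2.0 per SD for stay, power without adjustment is 90%, 86%, 79% or 71%. With adjustment it is about 88% to 91%. The unadjusted hazard ratio moves to 1.20, 1.19, 1.17 or 1.15. Here adjustment changes the quantity estimated as well as the power.

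**The case against.** The strongest reply is that nothing here is wrong. Adjusting for the factors used in minimisation is standard, and a randomised comparison needs no further covariate to be valid. That stands.

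A reader might infer that the omission biases the result or leaves chance imbalance uncorrected. The documents do not support this. Imbalance averages to zero and is already part of the confidence interval; the 1 to 2 point shift above is a 95% extreme under assumed risks.

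A second reply is that the article leaves to the analysis plan the detail of methods, "including any adjustments for covariates and multiple comparisons". That plan is not at hand and may add FiO2. This weakens the point but does not remove it, because the article already names the primary adjustment set and rests primary inference on it. An analysis plan that adds FiO2 to the primary model would need reconciling with this text.

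Third, the size is assumed throughout. The article gives neither event risk by entry FiO2 nor the share entering by each route. The lower-FiO2 route also requires work of breathing, so it is selected for severity on another axis and the gradient between strata may be shallow. The article does not say that the numerical FiO2 is stored. All of this stands, and it is why a range is shown and a stratum fallback is offered.

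Finally, it is tempting to claim the same benefit for both primary outcomes at no cost. The baseline-of-the-outcome argument applies only to severe respiratory failure. Nothing in the documents shows that entry FiO2 predicts length of stay.

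**Conclusion.** The point holds as an improvement, not as the correction of an error. For severe respiratory failure, the stated primary model omits the baseline value of the outcome's own scale, although that value must be known to confirm eligibility. The analysis remains unbiased and the stated sample size reproduces.

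The gain forgone is about 0.5 to 5 power points at a 45% control rate, and from almost nothing to about 3.6 points at 25%. The upper ends need an odds ratio of 3 per SD. These figures assume an effective 1280 infants and take no account of what gestation and centre already explain. With moderate to strong prognosis, the gain would recover much or all of the shortfall to 90% seen at the lower event rates with 640 per arm. With weak prognosis it would be negligible.

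The target of inference need not change. The risk ratio and risk difference are collapsible, so adding the covariate does not in itself alter the effect being estimated. This is not so for the hazard ratio in the length-of-stay model.

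**What to change.** Before database lock, pre-specify FiO2 at randomisation as an added covariate, alongside the minimisation factors, in the primary model for severe respiratory failure. Use it as a continuous variable if the value is recorded. Otherwise use the eligibility stratum: below 0.30 with work of breathing versus 0.30 to below 0.45. Keep the model with minimisation factors only as a supporting analysis. Align the article, the full protocol and the analysis plan on which model carries the primary inference.

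For length of stay, treat the addition as optional. If it is made, say that the hazard ratio is then conditional on FiO2.

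Minimisation need not change. The cost is a sentence or two of analysis-plan wording, one more covariate, and a stated rule for infants with no recorded FiO2, since no imputation is planned and they would otherwise drop out of the model. Because the trial is open-label, the choice is credible only if it is fixed before outcomes are compared by arm.
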